#### **4.2.8. Meal challenge (IV)**

All individuals will be asked to consume two different meals, an high fat/high energy meal and another low fat/low energy. The high-fat/high energy meal will by characterize by: total energy (TE) approximately of 1600kcal, consisted of 40g protein (9,6% TE), 218g carbohydrate (55% TE), and 60g total fat (34% TE) and 18g saturated fat (10% TE). The other meal will be according to the Portuguese guide - Roda dos Alimentos[58], characterized with low-fat/low energy meal: TE approximately with 660kcal (1/3 of 2200kcal), consisted of 50 to 70% TE of carbohydrate, 30% TE of total fat and less than 10% of saturated fat.

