Relationship between physical fitness, diet, exercise and immune suppression has been mainly studied in athlete or highly physically active population as reported in the recent published systematic review of Gunzer et al[4]. No conclusion has been withdrawn due to limited research evidence on how to reduce post-exercise upper respiratory symptoms with single macronutrients, namely in high fat nutrition meals [4]. In asthma patients a recent randomizes study by Wood et al, non-obese subjects with asthma were compared with obese subjects who were submitted to a high fat meal challenge versus a low fat meal. It was shown that the participants allocated to the high fat meal showed 4h post-meal an increase in sputum neutrophil percentage, toll-like receptor 4 and a lower relationship of FEV1/FVC, thereby relating the fat consumed to an increase inflammation status. In another study by Meksawan, sedentary men (n=5) and women(n=6) had dietary fat intake during 3 weeks (19% calories and 50% calories) followed by an acute maximal exercise effort test. Evaluated inflammatory mediators of the immune system associated the bout of exercise to an increase of pro-inflammatory mediators which was aggravated by the fat meal for the previous 3 weeks in comparison with normal fat or high fat diet in this study the increase in pro-inflammatory mediators were not seen with a 50% caloric balance.

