### **3. RESEARCH QUESTION AND AIMS**

The research question of this project is: how physical activity and diet interfere with the immune system functions, namely respiratory infection susceptibility and illness prone profile.

The main outcomes are:

- Evaluate the use of a respiratory infections questionnaire to diagnose and characterize respiratory infections and their impact on lives in Portuguese patients with respiratory infections over 16 years old. Perform a cross-cultural translation and validation of WURSS-21;
- Evaluate the upper respiratory tract infections risk factors (demographics, fitness profile, inflammatory, metabolomic, neuro-endocrine and environment) in a population with a high level of exercise intensity;
- Test the effect of a controlled, moderate intensity long-term training program in an elderly population;
- Evaluate the effect of a high fat meal compared to a healthy diet meal on the neuro-immune-endocrine response to exercise;
- Study the effect of physical activity reduction on neuro-immune-endocrine mediators and respiratory infections.

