## **10. EXPECTED RESULTS AND OUTCOMES**

### **Expected results**

To obtain a valid method for upper respiratory infections assessment that will permit its monitoring in the clinical and experimental setting.

To evaluate the risk factors related with respiratory infections in a athletes population, namely physical fitness, nutrition and stress showing the multi-factorial side of immunosuppression in high intensity exercise.

To assess risk of respiratory infections in a physical activity and inactivity intervention as well as immune mediators impact. Evaluate the interference of high fat diet previously to acute exercise challenge and demonstrate the effect of this association in immune system in a particularly susceptible population (asthma-obese patients). This will permit to understand the effects of exercise in the immune system allowing physicians and trainers to adapt its intensity to specific populations.

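### Study IV's two meals differ mainly in size, so the comparison is valid for the whole meals but a difference cannot be attributed to fat

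*Protocol*

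**What the plan says.** Section 4.2.8 defines the two meals. The high-fat one has "total energy (TE) approximately of 1600kcal"; it "consisted of 40g protein (9,6% TE"), "218g carbohydrate (55% TE), and 60g total fat (34% TE) and 18g saturated fat (10% TE"). The other follows the Portuguese food guide. It has "TE approximately with 660kcal (1/3 of 2200kcal") and "consisted of 50 to 70% TE of carbohydrate, 30% TE of total fat and less than 10% of saturated fat".

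The question is put in terms of fat in most places. Section 3 gives the aim as: "Evaluate the effect of a high fat meal compared to a healthy diet meal on the neuro-immune-endocrine response to exercise". Section 10 expects to: "Evaluate the interference of high fat diet previously to acute exercise challenge". The heading and text of section 4.1.4, the Rationale (section 1) and the aims in the English Summary also name fat alone.

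Elsewhere the wording is wider. The methods part of the English Summary and the opening of section 4.2.8 label the meals by fat and energy together. The Portuguese summary calls the diet and the meal *hipercalórica*, that is, high in calories.

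Section 4.3.3 compares the two meals by paired t-tests and repeated-measures ANOVA. There is no third meal and no comparator matched for energy or carbohydrate.

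**The concern.** A cross-over with two meals yields one contrast. Whatever differs between the meals is bundled into that contrast. Here the meals have nearly the same proportions, and one is more than twice the size of the other, so fat, carbohydrate and total energy all rise together.

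A difference in immune markers after exercise could come from any of the three. If it is reported under the present aim, it will be read as an effect of dietary fat in asthmatic and obese people, for whom the Rationale hopes to issue recommendations. What is at stake is the interpretation of the result; the conduct of the comparison is not in question.

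**Working it through.** **Inputs.** All come from section 4.2.8, except the energy factors of 4 kcal/g for protein and carbohydrate and 9 kcal/g for fat. Those are an assumption, tested in step 1.

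**1. Reproduce the plan's shares for the high-fat meal.**
- Protein 40 × 4 = 160 kcal; carbohydrate 218 × 4 = 872; fat 60 × 9 = 540; sum 1572 kcal. Saturated fat 18 × 9 = 162 kcal.
- Over 1600 kcal: carbohydrate 54.5%, fat 33.75%, saturated fat 10.1%.
- Over 1572 kcal: carbohydrate 55.5%, fat 34.4%, saturated fat 10.3%.
- These match the stated 55, 34 and 10%, so the factors are adequate. Protein comes to 10.0% of 1600 kcal against the stated 9.6%, a small slip with no bearing here.

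**2. Convert the comparator's shares to grams, at 660 kcal.**
- Fat: 0.30 × 660 = 198 kcal; 198 / 9 = 22 g.
- Carbohydrate: 0.50 × 660 = 330 kcal = 82.5 g, up to 0.70 × 660 = 462 kcal = 115.5 g. At the upper end nothing is left for protein (100 − 30 − 70 = 0%), so that end is a limit.
- Saturated fat: under 66 kcal, or 7.3 g.

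**3. Check the comparator's energy.** 660 / 2200 = 30%, whereas 2200 / 3 = 733 kcal. The figure and its gloss disagree, so both are carried forward.

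**4. Contrast between the meals, high-fat meal at 1600 kcal.**

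| | Comparator 660 kcal | Comparator 733 kcal |
|---|---|---|
| Energy ratio | 2.42 | 2.18 |
| Energy gap, kcal | 940 | 867 |
| Fat, g | 60 v 22 | 60 v 24.4 |
| Fat difference, kcal | 540 − 198 = 342 | 540 − 220 = 320 |
| Fat ratio | 2.73 | 2.45 |
| Carbohydrate, g | 218 v 82.5–115.5 | 218 v 91.7–128.3 |
| Carbohydrate difference, kcal | 410–542 | 359–505 |
| Carbohydrate ratio | 1.89–2.64 | 1.70–2.38 |
| Fat, part of energy gap | 36% | 37% |
| Carbohydrate, part of energy gap | 44–58% | 41–58% |

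Using the summed 1572 kcal in place of 1600, with the 660 kcal comparator, gives an energy ratio of 2.38, with fat at 37.5% and carbohydrate at 45–59% of a 912 kcal gap. The picture does not change.

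**5. How much of the fat difference is composition and how much is size?** Scale the comparator's 30% share up to 1600 kcal: 0.30 × 1600 / 9 = 53.3 g. Of the 38 g difference in fat (60 − 22), 53.3 − 22 = 31.3 g (82%) comes from the larger portion and 60 − 53.3 = 6.7 g (18%) from the higher share.

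**6. Can the planned analysis separate them?** Each participant has one value per meal, and meal is the only randomised factor. Paired t-tests and repeated-measures ANOVA estimate the effect of the whole meal. Section 4.1.4 has food left on the plate recorded, but variation in leftovers is not randomised and cannot identify a separate effect of fat.

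**The case against.** The strongest reply is that the Protocol never claims to isolate a nutrient. The methods part of its English Summary and section 4.2.8 name energy beside fat, the Portuguese summary speaks of calories, and section 3 sets the high-fat meal against a healthy-diet meal, which is a whole-meal comparison. Absolute fat does nearly triple. A test of a realistic large meal against a guide-based one is a legitimate design.

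Most of that stands. A reader might infer that Study IV cannot answer its question at all. The documents do not support this: the randomised within-person comparison of the two meals is valid. What survives is that several sections drop energy from the label and present the contrast as one of fat.

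Three further inferences go too far:
- That carbohydrate differs more than fat. This holds in grams and kilocalories. As a ratio, fat changes more (2.73-fold against 1.89–2.64-fold).
- That the background studies varied the fat share. Section 2 reports shares for only one, a three-week diet study whose participants "had dietary fat intake during 3 weeks (19% calories and 50% calories"). It gives no composition for the meal challenge in asthma.
- That the plan treats carbohydrate as a driver of IL-6, so that it might mask a fat effect. The sample size text in section 4.3.3 takes only a standard deviation from a carbohydrate study and says it does not generalise to this population. The Protocol gives no direction or size for such an effect.

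**Conclusion.** The point holds as one of attribution. The two meals have similar energy shares (fat 34% against 30%, saturated fat about 10% against under 10%) and differ mainly in size: 2.4-fold in energy at 660 kcal, 2.2-fold at 733 kcal. Fat contributes 36–37% of the energy gap and carbohydrate 41–58%, with the high-fat meal at 1600 kcal. Fat is therefore confounded with energy and carbohydrate, and a difference between meals cannot be credited to fat as sections 1, 3, 4.1.4 and 10 would have it. The comparison of the two whole meals remains sound.

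This rests on the section 4.2.8 figures and on the 4/4/9 energy factors, which reproduce the plan's fat, carbohydrate and saturated fat shares. It does not depend on which comparator energy is meant or on where carbohydrate falls within 50–70%.

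**What to change.** 1. Bring the study title, the aim (English Summary and section 3), the Rationale (section 1), section 4.1.4 and the expected results (section 10) into line with the combined fat-and-energy label in the methods part of the English Summary and in section 4.2.8, and with the Portuguese summary.
2. State that the conclusion will concern a large high-energy mixed meal against a guideline-based low-energy meal, with no attribution to fat alone.
3. Reconcile the comparator's 660 kcal with its description as one third of 2200 kcal.

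The cost is rewording. No visits, participants or assays are added. The downside is a narrower claim.

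If the sponsor wants a conclusion specific to fat, the meals would have to differ in fat share at equal energy. That is optional, and a choice for the sponsor and the nutritionists who build the meals. It would test a different question and give up the comparator's guide-based portion size.

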#### **4.2.9. Exercise challenge (IV)**

Protocol will be performed accordingly as previously published and aimed to access physical fitness, exercise induced bronchoconstriction [59, 60].

Contra-indications to perform exercise testing will be: moderate to severe airflow limitation (predicted FEV1<60% or <1,5L), heart attack or stroke in the last 3 months, uncontrolled hypertension (systolic BP>200 or diastolic BP>100), malignant arrhythmias, know aortic aneurysm, orthopedic limitations to exercise, inability to perform acceptable-quality spirometry, pregnancy, nursing mothers, current use of cholinesterase inhibitor medication (myasthenia gravis).

The challenge will be performed in controlled conditions, ambient temperature between 20-25°C, with low relative humidity (less or equal to 50%). Heart rate will be monitored during all test by a reliable measurement (three lead electrocardiographic configuration or pulse oximeter), nasal clips will be used during the test and blood pressure will be taken before the challenge.

Exercise challenge will be done in a treadmill with starting with a slope of 5.3% and consists: in a 2 min warm up until the heart rate achieved 70-80% of the estimated HR peak, calculated as  $(220 - \text{age [years]})$ , (ventilation can also be used to monitor and should reach 40-60% of the predicted maximum voluntary ventilation, estimated by  $\text{FEV}_1 \times 35$ ). The speed will then be adjusted during the first 4 minutes to achieve a workload corresponding to the maximum speed subjects will be able to sustain for the last 4 min, about 95% of the estimated HR. This test usually requires 6 to 8 min, but longer period of time will be needed and will be adjusted to an individual basis and the patient physical condition. At the end of the test  $\text{VO}_2$ , VE, RER, and HR will be measured as well as lung function, namely maximal forced expiratory flow volume loops at 1, 3, 5, 10, 15 and 20 minutes after the challenge. In all patients bronchodilation with salbutamol will be performed after 15 min.

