#### **4.1.4. Effect of an high fat meal on neuro-immune-endocrine response to an acute exercise challenge (IV)**

This is a randomized cross-over trial, with a wash out period of 7 days, single-blinded, placebo controlled. Study design is specified in figure 1. Participants will be recruited from advertisement and four different groups will be compared: obese-asthmatic; asthmatic non-obese; obese without asthma and non-asthmatic and non-obese. Stratification will be done accordingly to having asthma and  $BMI \geq 30 \text{ kg/m}^2$ . All patients will be allocated to a meal challenge in which a high fat meal will be followed by a low fat meal or vice-versa, meal challenge order will be randomized and participants blinded to the intervention. Three hours after it will be followed by an exercise challenge, which is aimed to induce acute immune changes. The main outcome will be exercise-immune function (immune function markers) changes after a diet challenge. As secondary outcomes stress/inflammatory markers, endocrine mediators, as well as blood fatty acids will be measured. Lung function,  $VO_2$  and airway inflammation will be assessed by exhaled breath condensate inflammatory markers and eNO. Any adverse events of the challenge will be registered, namely respiratory infections, gastro-intestinal symptoms and muscular ache.

[figure not shown]

**Figure1.** Randomized cross-over study trial, single-blinded to meal intervention. Measures (1.1; 1.2;2.1;2.2) immediately before and after exercise challenge include: Immune-endocrine-metabolomic response (blood, urine and saliva samples); Pupilometry; Lung-function and VO2 consumption; skin prick histamine reactivity

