### Intervention:

Meal challenge will be of high fat and low fat meal. Both meals composition will be controlled and built by a nutritionist team. All food left in the plate will be evaluated and registered to understand the caloric ingestion of each participant. No restrictions will be imposed previously neither diet control, as acute changes are the main outcome of this study and a daily diet diary will be provided. Only patients with controlled asthma can start the intervention, in the day of the first challenge they will return the accelerometer.

After the meal challenge, participants will not be allowed to eat or drink, in exception to water, and cannot perform any physical exercise. Then they will be taken to an exercise challenge laboratory, at Sports Faculty of Porto University, there 3 hours after the meal challenge blood, urine sample and exhaled breath condensate will be collected, heart rate at rest registered, skin test reactivity with histamine and spirometry performed. Exercise challenge, after the measurements 1 or 2 (figure 1) will be done. During the exercise heart rate response, exhaled VO2, CO2 and symptoms will be systematically registered. A physician and a cardiopulmonary technician will follow the challenge. Immediately after, a spirometry will be done and then at 5, 10 and 15 min after stopping the run, induced bronchoconstriction, pupillometry will be also measured and skin test with histamine and new blood and urine samples will be taken. If a fall in FEV1 over 10% occurs, bronchodilation will be done and patient treated. The exercise challenge will take at minimum 8 min, and patient will be asked to perform maximum effort, as the aim is to maintain for 4 min the heart rate at 95% of the target heart rate (220-rest heart rate).

Blood, exhaled air condensate, urine and saliva obtained before and after the exercise challenge will be used to analyze: metabolomic markers, immune function and inflammatory measures (in ex. leukocytes, lymphocytes, neutrophils, lymphocytes subpopulations and cytokine reduction, like IL-1, IL-6 and IgA in the saliva), stress mediators/hormones (ex. blood cortisol, growth hormone and epinephrine), endocrinological markers (ex. insulin, resistin, adiponectin, PAI-1, leptin) and fatty acids level (ex. monounsaturated, polyunsaturated and saturated fatty acids). Skin test sensitivity will be evaluate by histamine reactivity.

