Exercise testing (IV), namely maximal symptom-limited exercise testing is a relatively safe procedure, especially in otherwise healthy individuals. Fatality risk is related to medical complications to the underlying disease and the rate of death per patients during exercise testing is 2 to 5 per 100.000[75]. Strict contra-indications will be followed. A licensed physician and an cardio-respiratory technician will observe the participant during exercise and the recovery period and watch for undue stress (e.g., severe wheezing, chest pain, lack of coordination) or adverse signs (e.g., ECG abnormalities, falling blood pressure, decrease in O2 saturation), if it occurs the test will be immediately stopped and any adverse event treated. A resuscitation cart will be immediately available. The population tested in this study will be young and otherwise healthy without know disease, only chronic co-morbidity will be asthma and obesity. Exercise induced bronchoconstriction is assessed by exercise challenge and it is a recommended and widely used method to evaluate asthma patients. Furthermore these population will be under controlled asthma. If any adverse event occurs, namely bronchoconstriction it will be immediately reversed with bronchodilation.

Exercise intervention in the elderly population (III), was already submitted and accepted by the ethical commission (**Attachment 6**). Moderate exercise program will be performed and adapted to each elderly participant, co-morbidities and difficulties and physical condition and anaerobic resistance for exercise strength will be evaluated previously to the training by resistance maximum. Exercise will then be adapted to each individual condition and progressively increased at each participant rhythm. The exercise will be guided by sports professors trained in exercise teaching and monitoring. Potential adverse conditions can occur, namely muscle and body ache which will be self-limited and prevented by this progressive adaptation to exercise. All elderly will have an individual insurance if any adverse event occurs, namely falls during training or any unavoidable accident.

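### Study IV's maximal treadmill test may be monitored by ECG or pulse oximeter alone, so a team can lack one of the signals that the safety section names as a reason to stop

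*Protocol*

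**What the plan says.** Section 4.2.9 (exercise challenge, study IV) sets the monitoring. Heart rate is followed throughout the test by one of two devices, and the sentence goes on to time the blood pressure reading: "three lead electrocardiographic configuration or pulse oximeter), nasal clips will be used during the test and blood pressure will be taken before the challenge". After the run the section lists gas-exchange measures, heart rate and lung function, the last as "maximal forced expiratory flow volume loops at 1, 3, 5, 10, 15 and 20 minutes after the challenge".

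Section 4.1.4 (Intervention) asks for maximum effort. During the run, heart rate, oxygen uptake, carbon dioxide "and symptoms will be systematically registered". The Figure 1 legend says that the measurements "immediately before and after exercise challenge include: Immune-endocrine-metabolomic response (blood, urine and saliva samples); Pupilometry; Lung-function and" oxygen consumption, plus histamine skin reactivity.

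Section 5 (Safety, exercise testing) says that a physician and a cardio-respiratory technician "will observe the participant during exercise and the recovery period". What these two staff members are to look out for is then set down: "watch for undue stress (e.g., severe wheezing, chest pain, lack of coordination) or adverse signs (e.g., ECG abnormalities, falling blood pressure". A fall in oxygen saturation is the third instrument-based example. The consequence is firm: "if it occurs the test will be immediately stopped and any adverse event treated".

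**The concern.** The safety section supports its case that the test is acceptable partly by naming signs on which staff will stop it. Three of those signs cannot be judged by eye: an ECG abnormality needs an ECG, a fall in saturation needs an oximeter, and a fall in blood pressure needs repeated readings. The section that tells the laboratory what to attach and when to measure makes the first two alternatives and times the third only before the run.

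What is at stake is participant safety in a test that asks for maximum effort, with about 4 minutes near 95% of the estimated heart rate, done twice by each participant. Some of those participants have asthma, obesity or both. The estimate of the meal effect is not at stake.

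**Working it through.** No figure in the plan needs reproducing for the main point. The check sets the signs named in section 5 against each set-up that section 4.2.9 allows.

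| Set-up under section 4.2.9 | ECG abnormality | Drop in saturation | Fall in blood pressure |
|---|---|---|---|
| Pulse oximeter only | not seen | seen | no reading scheduled after the start |
| Three-lead ECG only | seen | not seen | no reading scheduled after the start |
| Both (allowed, not required) | seen | seen | no reading scheduled after the start |

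A single device covers 1 of the 3 instrument-based signs, and both together cover 2 of 3.

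**Does another section fill the gap?** Four lists describe measurements around the run: the Figure 1 legend, the list during the run in section 4.1.4, the list after the run in the same section, and the end-of-test list in section 4.2.9. None names ECG, saturation or blood pressure during exercise or recovery. For study IV, the other mention of an ECG is the screening exclusion in section 4.1.4 (Participants), and the other mention of blood pressure is the baseline assessment in section 4.1.4 (Procedures).

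**Number of tests.** Each participant runs twice. Section 4.3.3 plans 30 participants, so 2 × 30 = 60 tests. The Summary mentions 60 in total, so 2 × 60 = 120 tests.

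**Absolute risk.** Section 5 cites 2 to 5 deaths per 100,000 patients tested.

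- Applied to each test: 60 × 2/100,000 = 0.0012, and 120 × 5/100,000 = 0.006.
- Applied to each participant: 30 × 2/100,000 = 0.0006, and 60 × 5/100,000 = 0.003.

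The per-test count is the more cautious of the two.

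**Recovery time points already in place.** Section 4.2.9 has flow-volume loops at 1, 3, 5, 10, 15 and 20 minutes. Section 4.1.4 has spirometry immediately after the run and at 5, 10 and 15 minutes. The two share 5, 10 and 15 minutes.

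**The case against.** The strongest reply is that the *or* in section 4.2.9 concerns only how heart rate is measured and does not limit other safety monitoring. Section 5 binds separately, so a team that cannot see the named signs falls short of section 5 whatever section 4.2.9 allows. This is right as far as it goes, and for that reason a reader should not infer that the two sections contradict each other. A team can satisfy both. But section 5 names no device, while section 4.2.9 does and treats either as enough. Staff who prepare the test from the procedure section could comply with it and still lack a signal that section 5 relies on.

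Second, the signs are introduced as examples, and section 4.2.9 refers to published methods that may specify more monitoring. Both points stand. The examples are not a checklist, and the lack of blood pressure readings after the start is a fact about the protocol text, not proof that none will be taken. The protocol itself, however, states a device choice and a blood pressure time.

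Third, risk is low and other safeguards are substantial: a target age of 18 to 35, exclusion for an abnormal screening ECG, arrhythmia, angina or heart failure, listed contra-indications, a physician and technician present, stopping for visible distress, treatment of an FEV1 fall over 10%, and a resuscitation cart. This stands and limits the weight of the point.

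Fourth, cuff readings taken after the run cannot stop it. This also stands, and the fix treats them as recovery monitoring only.

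**Conclusion.** The point holds in a limited form. Section 4.2.9 permits a maximal test with ECG or pulse oximetry alone, so the ECG or the saturation signal that section 5 gives as an example of a reason to stop may be missing. Blood pressure is a secondary gap: the text schedules no reading from which a fall during the run could be seen.

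The documents do not support a reading that the test is unmonitored or unsafe. Expected deaths are about 0.001 to 0.006 over 60 to 120 tests. This assumes that the cited general rate applies to each test. The protocol gives no rate for exercise after a high-fat meal and says that this combination has not been studied in this population. Nor does the point touch the endpoints, the analysis or the comparison of meals. It is a cheap safety improvement that should be made, not a flaw in the trial's inference.

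**What to change.** **Main change.** In section 4.2.9, replace *or* with *and*, so that three-lead ECG and pulse oximetry both run through exercise and recovery.

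**Secondary change.** Add cuff readings immediately after stopping and at 5 and 10 minutes, when spirometry is already scheduled, and call them recovery monitoring. If falling blood pressure is to remain a reason to stop the run, section 4.2.9 must also schedule at least one reading during exercise. Without that reading, section 5 should describe a fall as a recovery criterion.

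**Cost.** Both devices are already named and a technician is already present, but the protocol names the devices as alternatives, so it is an assumption that the laboratory has both. Three recovery readings per test come to 3 × 60 = 180, or 3 × 120 = 360. One reading during exercise would add 60 to 120. The recovery readings leave the final 4 minutes at target load undisturbed; a reading during the run should be timed with that in mind.
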